**Enrolment**						
Information/eligibility screen	✓					
Standardised questionnaire^a^	✓		✓	✓	✓	✓
MMSE^b^	✓					✓
Consent signature		✓				
**Intervention**		✓	✓	✓	✓	✓
**Assessment**						
SF12 and EQ-5D-3 L Questionnaires^c^		✓	✓	✓	✓	✓
Clinical examination^d^	✓	✓	✓	✓	✓	✓
Biological tests^e^	✓(*)		✓	✓	✓	✓
ECG^f^		✓		✓	✓	✓
Clinical event data collection^g^		✓	✓	✓	✓	✓
Compliance^h^		✓	✓	✓	✓	✓
CVRF collection^i^		✓	✓	✓	✓	✓
SE/SAE collection ^j^		✓	✓	✓	✓	✓

^a^Standardised questionnaire with six questions to search for coronary disease history, stroke, or unnoticed peripheral artery disease

^b^Mini-Mental State Examination (French version, GRECO)

^c^Quality of Life Questionnaire SF12 (self-administered) and EQ-5D 3 L (self-administered)

^d^Clinical examination: examination as recommended by good clinical practices in the field of cardiovascular medicine (blood pressure, cardiovascular (CV) data, and lung auscultation)

^e^Laboratory tests: lipid (EAL), blood glucose, HbA1c (if diabetic), electrolytes, creatinine, creatinine clearance, and serum albumin. *In the absence of a balance sheet dated within 12 months before pre-inclusion, laboratory tests are prescribed at pre-inclusion and should be performed until the day of the inclusion visit

^f^ECG: electrocardiogram based on recommendations (once every 3 years if permanent arterial hypertension (HTA) and once a year if overt diabetes mellitus)

^g^Reports of significant clinical events occurring between visits

^h^Compliance assessed by Morisky questionnaire (eight items) at baseline (all patients) and during follow up (only in the group of patients in whom statin therapy is continued)

^i^Total CV risk factors: weight, waist circumference, smoking, hypertension, diabetes mellitus, previous family history of CV disease among first-degree relatives, high-density lipoprotein (HDL) and low-density lipoprotein (LDL) cholesterol

^j^SE/SAE: side effects and serious adverse events, respectively

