### Intervention

In the statin cessation strategy, the statins are stopped and patients are asked to end their treatment on the day of randomization. In the comparison strategy, patients continue their statin treatment at the usual dosage. Compliance with the use of statins is assessed by the Morisky questionnaire at each visit.

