### Randomization

Randomization is being carried out centrally using the e-CRF on the day of the visit for participant inclusion, after the participant has signed the consent form. Participants are considered enrolled in the trial when randomized.

The randomization is unbalanced, with a 5:4 ratio in favour of the statin-continuation group to take into account a 20% risk that patients allocated to the statin continuation group will stop statins after randomization for any reason (side effects, patient’s decision, physician’s decision). The allocation sequence was elaborated using computer-generated random numbers, and was not stratified. To reduce predictability of a random sequence, we used blocks of varying size. A document describing the randomization procedure is kept confidential within the Clinical Epidemiology Unit.

Taking statins or discontinuing statins will not require alteration to usual care pathways (including use of any medication) and these will continue in both trial arms. Participants in the statin discontinuation group who experience a new vascular event will be allowed to restart statins at the discretion of the investigator and according to good clinical practice.

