### Outcome measures

#### Economic endpoints

The cost-effectiveness of the statin cessation strategy compared to continuation of statins will be estimated based on the incremental cost per quality-adjusted life year (QALY) gained at 36 months, from the perspective of the French healthcare system. QALYs will be measured using the Euro-QOL five-dimension, three-level (EQ-5D-3 L) questionnaire at inclusion and at each follow-up visit [18]. This questionnaire has been validated in the French population.

Healthcare resources and costs will be extracted from the French Administrative Health Care Database (Système National des Données de Santé, SNDS) by a merging procedure, operated by the French National Health Insurance Fund and using data from the SITE trial. The SNDS gathers all reimbursement data for 98.8% of the French population [19]. The time horizon of the study (36 months) implies a discounting of costs and outcomes. In accordance with the methodological economic guidelines of the French National Health Authority (Haute Autorité de Santé, HAS), we will apply a 4% discount rate.

Following cost-effectiveness analysis (CEA), budget impact analysis (BIA) will provide useful information about the sustainability of the statin cessation strategy if it were applied to the entire French healthcare system. It will consider outpatient costs, hospital costs, medical and non-medical costs induced or avoided by stopping statins, and all budgetary implications related to changes in health management and/or health status improvement. The difference between induced and avoided costs will provide the net benefit to the healthcare system of widespread adoption of the statin cessation strategy for primary prevention among elderly individuals in France.

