### Statistical methodology

In the non-inferiority analysis, the bilateral 95% confidence interval (CI) for the between-group difference in the 3-year mortality rate will be estimated. Considering < 5% change as clinically non-significant, we will consider non-inferiority demonstrated only if the 95% CI upper bound of the 3-year mortality difference between the two groups is < 5%. This analysis will primarily be performed according to an under-treatment principle. Formally, patients who do not receive the trial treatment as planned in the protocol will be excluded from the analysis. An intention-to-treat analysis will also be performed with the aim of maintaining the initial effect of randomization. The “missing = failure” strategy (failure being defined as death) will be used in the non-inferiority analysis.

Secondary clinical analyses will be conducted according to the intention-to-treat principle: all randomized patients will be analysed in the group to which they were initially randomized, and all of their data will be used regardless of eventual treatment changes during the study. As economic analysis is not based on statistical tests, no adjustment of the α-level is needed to deal with multiple comparisons. In all analyses, *p* < 0.05 will be taken to indicate statistical significance. A statistical team will analyse all data independently of the investigator.

The economic analysis will also be conducted according to the intention-to-treat principle. First, the point estimate of the incremental cost/utility ratio and its bootstrap 95% CI will be calculated. We will then estimate the incremental net monetary benefit (INMB) adjusted for potential confounding factors (adherence to statins at baseline, treatment duration, and particular statin dosage) using multiple linear regression models. Acceptability curves will then be plotted. The value of information will also be examined according to the principles proposed by Claxton [20].

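### The primary analysis excludes non-adherers in both arms, but by one of two conflicting statements the only adherence measure named after baseline covers the continuation arm alone

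*Protocol article*

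**What the plan says.** All references are to the protocol article.

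- Intervention: "Compliance with the use of statins is assessed by the Morisky questionnaire at each visit". No arm is singled out.
- Table 1, footnote h: the questionnaire is given to all patients at baseline, then "during follow up (only in the group of patients in whom statin therapy is continued".
- Statistical methodology, on the non-inferiority analysis: "This analysis will primarily be performed according to an under-treatment principle". The rule is that "patients who do not receive the trial treatment as planned in the protocol will be excluded from the analysis". A second analysis is planned: "An intention-to-treat analysis will also be performed with the aim of maintaining the initial effect of randomization".
- Randomization: "Participants in the statin discontinuation group who experience a new vascular event will be allowed to restart statins", at the investigator's discretion. No restart rate is given.
- Sample size: 20% stopping is allowed for in the continuation arm. Nothing is allowed for exclusions from the cessation arm.
- Economic endpoints: "The SNDS gathers all reimbursement data for 98.8% of the French population". The linked data serve resource use and costs. The Discussion adds one further use, checking for closer surveillance of cardiovascular events in the discontinuation group.
- Table 1 also ticks an unexplained Intervention row, laboratory tests including lipids, and clinical event collection at every follow-up visit, with no limit by arm. None of these is linked to membership of the primary analysis set.

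**The concern.** The exclusion rule works only if the treatment actually received is known in both arms, and to the same standard. Under footnote h, the named instrument can reveal stopping in the continuation arm, while nothing named reveals restarting in the cessation arm. A patient who stops in one arm could then leave the primary set, while a patient who restarts in the other stays in it as a patient who stopped statins.

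Extending the Morisky scale to both arms would not cure this. It asks how well a prescribed drug is taken, not whether a withdrawn drug has been taken up again.

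What is at stake is the meaning of the primary non-inferiority result. An under-treatment set is meant to remove the dilution caused by crossover. If it does so in one arm only, part of the dilution remains, and unequal selection is added in a trial where physician and patient know the allocation.

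**Working it through.** **1. The plan's own figure.** Inputs from Sample size: 15% mortality in both arms, 5-point margin, one-sided alpha 2.5%, power 90%.

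n per arm = (1.960 + 1.282)² × 2 × 0.15 × 0.85 / 0.05² = 1072, against 1080 stated. The continuation arm is 1080 / 0.80 = 1350, and 1080 + 1350 = 2430. The size reproduces and is not in error on this point. It leaves 1080 per arm in the primary set if 20% of the continuation arm is excluded and nobody is excluded from the cessation arm (power 90.2%).

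**2. Dilution from undetected restarts (illustration).** The documents give no restart rate r, so r is assumed. Also assumed: the true difference equals the 5-point margin, restarts happen early, none is detected, and restarters carry the continuation-arm risk of 15%.

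- Cessation-arm mortality: p = 0.20 − 0.05r
- Difference: d = 0.05(1 − r)
- SE = √{[0.15 × 0.85 + p(1 − p)] / 1080}
- One-sided error = Φ[(0.05 − d)/SE − 1.96]

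| r | p | d (points) | SE | One-sided error |
|---|---|---|---|---|
| 0% | 0.2000 | 5.00 | – | 2.5% |
| 5% | 0.1975 | 4.75 | 0.01627 | 3.5% |
| 10% | 0.1950 | 4.50 | 0.01623 | 4.9% |
| 20% | 0.1900 | 4.00 | 0.01614 | 9.0% |

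If restarts are instead spread evenly over the 3 years and excess risk is proportional to time off statin, the dilution roughly halves. Then r = 10% behaves like 5% (about 3.5%) and r = 20% like 10% (about 4.9%). Partial detection lowers the figures further.

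**3. Selection can work the other way.** Suppose there is no true difference, the 20% of stoppers are removed from the continuation arm, and nobody is removed from the cessation arm. If stoppers have relative mortality RR against the rest of their arm (assumed), the remaining continuation-arm mortality is 0.15 / (0.2 × RR + 0.8).

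| RR | Remaining continuation mortality | Artificial excess with cessation (points) | Power |
|---|---|---|---|
| 1 | 15.0% | 0 | 90.2% |
| 1.25 | 14.3% | 0.7 | 80.4% |
| 1.5 | 13.6% | 1.4 | 67.5% |
| 2 | 12.5% | 2.5 | 39.3% |

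This bias counts against non-inferiority, the opposite direction to step 2.

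**4. If restarters are found and excluded.** With 1080 patients left in the continuation arm, the cessation arm of the primary set and the power are: r = 5%, 1026 and 89.5%; r = 10%, 972 and 88.6%; r = 20%, 864 and 86.6%. The loss of power from proper ascertainment is modest.

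**The case against.** Four arguments on the other side carry weight.

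- Footnote h limits one questionnaire, not the recording of statin use. A drug-taking scale has little to measure in patients told to stop, and the Intervention sentence directly follows the description of the continuation strategy, so footnote h may simply specify it. This is a fair reading, but the text as printed still conflicts, and no replacement measure is named for the cessation arm.
- A reader might infer that restarters cannot be found. The documents do not support that. Reimbursement data can show statin dispensing in either arm, lipids are measured in both, the referent GP often follows the patient, and the unexplained Intervention row may hold treatment status. What stands is narrower: none of these is given the task of defining the primary set.
- A reader might also infer that the analysis is biased towards non-inferiority. That is not established either. The one restart route described follows a vascular event. Such patients may well have raised mortality, so keeping them in could work against non-inferiority and excluding them could favour it. Frailer stoppers removed from the continuation arm also work against it.
- Rules for a per-protocol set and e-CRF items commonly sit in the SAP or full protocol, neither of which is shown. Silence alone would be no finding. Here, however, the article states a one-arm measurement rule beside a two-arm exclusion rule, and contradicts itself on the former.

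The planned intention-to-treat analysis is free of unequal exclusion. It is still diluted by crossover, so it complements the primary analysis rather than repairing it.

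**Conclusion.** The point holds in limited form. The Intervention section and footnote h conflict. Under footnote h, exclusions from the primary set rest on a named measure in one arm and on no stated source in the other, so they may be ascertained unequally.

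The error rates of about 3.5%, 4.9% and 9.0% come from an assumed 5%, 10% or 20% of early, wholly undetected restarts at continuation-arm risk, with a true excess exactly at the margin. They show the size that dilution alone could reach; they are not estimates for this trial. The sign of the net bias is open.

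The matter should be settled before membership of the primary set is determined, since the main clinical conclusion depends on it.

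**What to change.** 1. Reconcile the Intervention section with Table 1 footnote h.
2. Define treatment received in both arms by one identical rule based on statin dispensing in the SNDS linkage, for example the date of first deviation judged by number of dispensings, fixed before outcomes are compared by arm.
3. At remaining visits, ask patients in both arms about any statin use since the last visit.
4. State whether a restart permitted after a vascular event under Randomization counts, for the analysis, as treatment received as planned.
5. Report the intention-to-treat result alongside the under-treatment result.

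The cost is one e-CRF question and wording in the protocol and SAP; the dispensing data come with a linkage already planned. There are limits. Recruitment began on 15 June 2016, so a new question cannot recover past visits, and for those the dispensing rule has to carry the weight. Patients who cannot be linked rely on self-report. If trial coverage matched the 98.8% national figure (an assumption), that would be about 0.012 × 2430 = 29 patients, plus any linkage failures. Dispensing also shows supply rather than intake, but equally in both arms.

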### Sample size

According to data from the French National Institute for Statistics and Economic Studies (Institut National de la Statistique et des Études Économiques, INSEE) in the French population aged 75 years or older, we assume that mortality at 3 years in both study groups will be 15%.

The SITE sample size was computed to achieve 90% power in showing the non-inferiority of statin cessation in comparison to statin continuation, assuming a 2.5% unilateral *α* risk and a non-inferiority margin of 5% of the between-group difference in overall mortality at 3 years after randomization (nQuery Advisor software, v. 7.0). A 5% non-inferiority margin is fairly commonly reported in the literature, but 3-year follow up is not. This yields an annual non-inferiority margin of only 1.7%, which we think would be quite acceptable for the scientific community. We do not have to deal with multiple tests, as cost-effectiveness analyses do not require statistical testing [20].

We also assume that 20% of the individuals randomized to the statin-continuation group may spontaneously stop their treatment during follow up. Therefore, to ensure 90% statistical power in under-treatment analysis, it was decided to include 20% more individuals in the statin continuation group. In total, 2430 individuals will be enrolled in the SITE study, including 1080 in the statin cessation group and 1350 in the statin continuation group.

### Data management

The e-CRF is the primary data collection instrument for the study. Medical information for individual participants obtained as a result of this study is considered confidential, and disclosure to third parties is prohibited. The e-CRFs are labelled with a unique trial number.

Consent forms sent to Sponsors may contain patient identifiers for the purpose of monitoring, as described in the trial risk assessment. Such information will be stored in secure, locked storage. Monitoring is mainly performed through e-CRF and by telephone. However, on-site monitoring is performed after the 3-month follow up and after the last follow up in each of the recruitment sites. Auditing may be required by the Sponsor or by the French authorities (ANSM) and the process is independent from investigators and the Sponsor.

### Statistical methodology

In the non-inferiority analysis, the bilateral 95% confidence interval (CI) for the between-group difference in the 3-year mortality rate will be estimated. Considering < 5% change as clinically non-significant, we will consider non-inferiority demonstrated only if the 95% CI upper bound of the 3-year mortality difference between the two groups is < 5%. This analysis will primarily be performed according to an under-treatment principle. Formally, patients who do not receive the trial treatment as planned in the protocol will be excluded from the analysis. An intention-to-treat analysis will also be performed with the aim of maintaining the initial effect of randomization. The “missing = failure” strategy (failure being defined as death) will be used in the non-inferiority analysis.

Secondary clinical analyses will be conducted according to the intention-to-treat principle: all randomized patients will be analysed in the group to which they were initially randomized, and all of their data will be used regardless of eventual treatment changes during the study. As economic analysis is not based on statistical tests, no adjustment of the α-level is needed to deal with multiple comparisons. In all analyses, *p* < 0.05 will be taken to indicate statistical significance. A statistical team will analyse all data independently of the investigator.

The economic analysis will also be conducted according to the intention-to-treat principle. First, the point estimate of the incremental cost/utility ratio and its bootstrap 95% CI will be calculated. We will then estimate the incremental net monetary benefit (INMB) adjusted for potential confounding factors (adherence to statins at baseline, treatment duration, and particular statin dosage) using multiple linear regression models. Acceptability curves will then be plotted. The value of information will also be examined according to the principles proposed by Claxton [20].

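### The primary non-inferiority analysis excludes patients for leaving their strategy after randomization, and intention-to-treat has no part in the decision, so bias is uncontrolled in direction and size

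*Protocol article*

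**What the plan says.** The Statistical methodology section of the protocol article makes the under-treatment analysis the primary one and defines it by exclusion: "Formally, patients who do not receive the trial treatment as planned in the protocol will be excluded from the analysis". Non-inferiority is declared if the upper bound of the two-sided 95% interval for the 3-year mortality difference is below 5%. An intention-to-treat analysis is also to be run, but no rule gives it a part in the claim. In the same analysis, missing outcomes count as deaths.

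The Sample size section shows that the exclusion covers events after randomization: "We also assume that 20% of the individuals randomized to the statin-continuation group may spontaneously stop their treatment during follow up". The continuation arm is enlarged to 1350, against 1080 for cessation, to keep 90% power in the under-treatment analysis. The Randomization section gives the reasons for stopping as side effects or a decision by the patient or physician. It says nothing on timing or prognosis.

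For the other arm, the Randomization section states: "Participants in the statin discontinuation group who experience a new vascular event will be allowed to restart statins at the discretion of the investigator". The article does not say whether such a restart counts as treatment as planned.

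**The concern.** Whole patients leave a mortality comparison because of something that happens during the three years in which mortality is counted. A patient who dies early has had little time to stop and stays in the set. A patient who survives three years has had the whole period in which to be excluded. Selection on survival therefore arises even when stopping has nothing to do with health, and it raises mortality in what is left of the arm. If patients stop because they are declining, selection works the other way.

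The decision rests on this set alone, so the true error rate and power depend on when and why patients stop, which the protocol neither states nor controls. At stake is either a false statement that stopping statins is safe to within 5 points, or a trial that has lost much of its planned power.

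**Working it through.** **Inputs from the Sample size section:** one-sided α 2.5%; power 90%; 3-year mortality 15% in both arms; margin 5 points; 20% stopping in the continuation arm; 1080 cessation and 1350 continuation patients.

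**Assumptions not in the article:** constant death hazard; constant stopping hazard unrelated to prognosis; stopping itself does not change mortality; no exclusions in the cessation arm; no missing vital status (so the missing-as-death rule is not exercised); unpooled normal interval.

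**Step 1, the plan's own figure.** n per arm = (1.960 + 1.282)² × 2 × 0.15 × 0.85 / 0.05² = 1072, close to the stated 1080. Power at 1080 per arm is 90.2%. Then 1080 / (1 − 0.20) = 1350. The sample size reproduces, and it confirms that 20% of the continuation arm is expected to be excluded.

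**Step 2, mortality in the retained continuation patients.**
- Death hazard λ = −ln(0.85)/3 = 0.0542 per year.
- Stopping hazard μ solves μ/(λ+μ) × (1 − e^(−3(λ+μ))) = 0.20, which gives μ = 0.0811 per year.
- Alive and still on statins at 3 years: e^(−3 × 0.1353) = 0.6664.
- Dead before stopping: (0.0542/0.1353) × (1 − 0.6664) = 0.1336.
- Retained: 0.1336 + 0.6664 = 0.80.
- Mortality among the retained: 0.1336/0.80 = 16.7%, against 15% in the arm as randomized.
- Mortality among stoppers: (0.15 − 0.1336)/0.20 = 8.2%.

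**Step 3, false non-inferiority at the margin (cessation 20%, continuation 15%).** The expected observed difference is 20 − 16.7 = 3.3 points. SE = √(0.167 × 0.833/1080 + 0.20 × 0.80/1080) = 0.01664. The probability of a claim is Φ((0.05 − 0.033)/0.01664 − 1.96) = Φ(−0.94) = 17.4%. Simulation of 20,000 trials also gave 17.4%. Without the distortion it is Φ(−1.96) = 2.5%.

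**Step 4, how far this depends on the assumptions.** All rows have 20% stopping in the continuation arm. Where stoppers' own mortality m is set, retained mortality is (0.15 − 0.20m)/0.80.

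| Scenario | False non-inferiority |
|---|---|
| All stop within the first 3 months | 3.1% |
| All stop within the first year | 5.4% |
| Constant rate over 3 years (steps 2 and 3) | 17.4% |
| Uniform over 3 years | 18.5% |
| Constant rate, 5% of cessation arm also excluded in the same way | 10.7% |
| Constant rate, 10% of cessation arm also excluded | 5.9% |
| Constant rate, 20% of cessation arm also excluded | 1.3% |
| A frail fifth (death hazard ratio 3) stops 3 times as often | 10.2% |
| Stoppers' 3-year mortality 10% | 11.4% |
| Stoppers' 3-year mortality 15% (break-even) | 2.5% |
| Stoppers' 3-year mortality 20% | 0.3% |

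In the last row retained mortality is (0.15 − 0.20 × 0.20)/0.80 = 13.75%, and power when both arms truly have 15% falls from 90.2% to 70%.

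**Step 5, requiring both analyses to succeed.** In the scenario of steps 2 and 3, simulation gave 2.5% error for the as-randomized difference and 92.8% power under equality. Intention-to-treat alone, with 1350 and 1080 patients, has 2.5% error and 92.9% power.

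**The case against.** The strongest objection concerns direction. A reader might infer that the rule necessarily inflates continuation mortality and so favours cessation. The documents do not support that. It holds only if stoppers have below-average 3-year mortality, and the article gives neither their timing nor their prognosis. Stopping that follows decline reverses the bias. This objection stands, and the 17% is one scenario near the upper end of those tabulated.

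Nor is the distortion shown to be confined to one arm. Enlarging the continuation arm protects power; it does not say that no cessation patient will be excluded, and comparable losses there offset the bias. A reader might also infer that permitted restarts add to it by removing high-risk patients from the cessation arm. But a restart that the protocol allows may count as treatment as planned, in which case nobody is removed. The article gives no restart rate and no mortality for such patients, so no size can be attached.

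It can also be said that on-treatment primacy was deliberate and sized for, that intention-to-treat results will be visible beside it, and that a joint rule is commonly left to an analysis plan. Visibility is not a decision rule, however. The article does fix the decision: one analysis, one bound. The fault lies in that stated rule and is not a matter of missing detail.

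Finally, intention-to-treat is no complete remedy. If stoppers take on the cessation-arm hazard, continuation mortality as randomized becomes 15.6%, and the error for an on-treatment difference of 5 points is about 5.5%. That is a reason to keep both analyses, not to rely on either alone.

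**Conclusion.** The concern holds as one of uncontrolled bias. The primary analysis conditions on behaviour after randomization that requires survival, and the analysis that preserves randomization cannot block a claim. Under constant, non-informative 20% stopping with no cessation-arm exclusions, the false non-inferiority rate is about 17% instead of 2.5%. Changing only the timing of that stopping moves the rate between about 3% and about 19%. Exclusions in the cessation arm lower it, and above-average mortality among stoppers turns the problem into lost power. That the trial will in fact be biased towards non-inferiority cannot be concluded from the article. What can be concluded is that the stated 2.5% error and 90% power are not secured by the rule as written.

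**What to change.** In the Statistical methodology section, state that non-inferiority is claimed only if the upper 95% bound is below 5 points in both the intention-to-treat and the under-treatment analyses. This needs wording only, and no new patients. The cost is a claim that is slightly harder to win. If stoppers have above-average mortality, the joint rule does not restore the lost power, because the under-treatment analysis must still succeed.

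As a supportive on-treatment analysis, where departure dates are available, follow patients from randomization and censor at departure, with weighting for informative stopping, instead of deleting them. State how this combines with counting missing outcomes as deaths. It should stay supportive: note h to Table 1 limits follow-up compliance data to the continuation arm, whereas the Intervention section has compliance assessed at each visit without that limit, so departure dates in the cessation arm are not assured. This part costs some programming and possibly a data item.

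Reconcile the Randomization and Statistical methodology sections on whether a permitted restart after a vascular event counts as a departure for analysis purposes.

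### Counting every patient with missing vital status as dead, in both arms, is not reliably conservative for the mortality non-inferiority analysis and makes the result sensitive to unequal loss to follow-up

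*Protocol article*

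**What the plan says.** Under Statistical methodology, the protocol article defines success as "non-inferiority demonstrated only if the 95% CI upper bound of the 3-year mortality difference between the two groups is < 5" per cent. The primary analysis excludes patients not treated as planned, and an intention-to-treat analysis is added. For missing outcomes one rule is given, a missing-equals-failure "strategy (failure being defined as death) will be used in the non-inferiority analysis". It is not limited to one arm or one analysis set, no rationale is given, and no other handling of missing vital status appears.

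Under Sample size, the design is "computed to achieve 90% power in showing the non-inferiority of statin cessation", "assuming a 2.5% unilateral" alpha, with "a non-inferiority margin of 5% of the between-group difference in overall mortality at 3 years after randomization". On the event rate, "we assume that mortality at 3 years in both study groups will be 15" per cent. The totals are 2430 patients, "including 1080 in the statin cessation group and 1350 in the statin continuation group". The 20% allowance there is for stopping statins in the continuation group. It is not an allowance for missing vital status, and no rate of loss to follow-up is stated.

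Under Main clinical endpoint, the GP investigators are the source of mortality data. The link to the national health data system (SNDS) is planned for resource use and costs (Economic endpoints) and for watching surveillance bias (Discussion). It is not named as a source of deaths.

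**The concern.** Counting missing as failure is cautious when the target is the failure rate of a single arm. Here the target is a difference between two arms that are imputed alike, and the aim is to show that this difference is small. Adding imputed deaths to both arms dilutes a real excess under cessation, which is the direction that favours the hypothesis. It also raises the event rate above the 15% on which the sample size was computed.

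If loss differs between arms, the imputed deaths enter the primary estimate directly. Patients and physicians know the allocation, so unequal loss is possible, and its direction cannot be known in advance. A non-inferiority claim on mortality could then be gained or lost through follow-up completeness and not through deaths. The intention-to-treat analysis is no independent check, because the rule covers the whole non-inferiority analysis.

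**Working it through.** **Inputs.** From Sample size and Statistical methodology: 15% mortality in both groups, 5-point margin, one-sided alpha 2.5%, 90% power, groups of 1080 and 1350. The primary set is taken as 1080 per arm (1350 × 0.80 = 1080 after the assumed stopping in continuation, nobody excluded from cessation). Missing rates are assumptions, because the article gives none. Within each arm, missingness is assumed unrelated to outcome.

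**Step 1: the plan's own figure.** n per arm = (1.960 + 1.282)² × 2 × 0.15 × 0.85 / 0.05² = 1072, against the stated 1080. Then 1080 / 0.80 = 1350. The sample size is reproduced. At 1080 per arm the SE is √(2 × 0.1275 / 1080) = 1.537 points and power is Φ(5/1.537 − 1.96) = 90.2%.

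**Step 2: effect of the rule.** In an arm with true mortality p and missing share m, counted mortality is p' = p + (1 − p)m.
- Equal m: the counted difference is (1 − m) times the true difference.
- Unequal m: each further point missing in an arm adds (1 − p) points to that arm, which is 0.85 at p = 15% and 0.80 at p = 20%.

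**Step 3: probability of declaring non-inferiority.** This is Φ((5 − d')/SE' − 1.96), where d' is the counted difference in points and SE' the unpooled SE at the counted rates. False non-inferiority is evaluated at a true 20% v 15%, power at 15% v 15%.

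Worked case, 5% missing in both arms:
- At the margin: counted 24.0% v 19.25%, d' = 4.75, SE' = 1.769, Φ(0.25/1.769 − 1.96) = 3.4%.
- With no true difference: counted 19.25% in both, SE' = 1.697, Φ(5/1.697 − 1.96) = 83.8%.

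| Missing, both arms | Counted difference when true excess is 5 points | False non-inferiority | Power |
|---|---|---|---|
| 0% | 5.00 | 2.5% | 90.2% |
| 1% | 4.95 | 2.7% | 88.9% |
| 2% | 4.90 | 2.9% | 87.6% |
| 5% | 4.75 | 3.4% | 83.8% |
| 10% | 4.50 | 4.5% | 78.2% |

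Binomial simulation with 400,000 runs per scenario agrees (3.5% and 4.6% error at 5% and 10%). The intention-to-treat set of 1080/1350 keeps about 87% power at 5% equal loss, with 3.5% error.

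**Step 4: unequal loss, 1080 per arm.**

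| Missing, lower v higher | Error if continuation has the higher loss | Power if cessation has the higher loss |
|---|---|---|
| 1% v 2% | d' = 4.10, SE' = 1.677: 7.7% | d' = 0.85, SE' = 1.588: 74% |
| 5% v 8% | d' = 2.20, SE' = 1.808: 34% | d' = 2.55, SE' = 1.737: 29% |

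**Step 5: comparison without imputation.** Analysing known vital status only, with 5% or 10% missing completely at random (1026 or 972 per arm), leaves the error at about 2.5% and power at 88.7% or 87.0%. Most of the power loss in Step 3 therefore comes from the imputation and not from the lost patients.

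**The case against.** The strongest reply is that loss of vital status may be very small. The endpoint is death, investigators are largely the patients' own GPs, eligible patients visit that GP regularly, sites are monitored after the last follow-up, and consent covers use of data after withdrawal. At 1% to 2% equal loss the error is 2.7% to 2.9% and power 88.9% to 87.6%, which is minor. This stands for equal loss. It does not answer a one-point imbalance at the same low level, and the amendment admitting patients from hospital departments weakens the reliance on GPs.

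A reader might infer that the rule always favours non-inferiority. It does not. Higher loss in cessation works against non-inferiority, and the larger variance costs power and partly offsets the shrinkage. At every equal rate tried, however, the error stays above 2.5%.

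A reader might also infer that the rule was chosen as a cautious one, or that nearly all patients lost are alive. The article gives no rationale and no information on the fate of lost patients. In this age group loss may be related to death, and if most of the missing had died the shrinkage argument would weaken.

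Nor does the three-month window around the 36-month close-out visit add to the problem. It is a visit window, whereas the endpoint is fixed at 3 years and deaths can be dated.

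Finally, sensitivity analyses are commonly left to an analysis plan that is not shown. That is fair, but the primary rule is stated here, and a later plan could repair the primary result only by contradicting it.

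**Conclusion.** The point holds in this form: the stated rule is not reliably conservative, and the primary result is sensitive to unequal loss. The direction follows from arithmetic, given loss unrelated to outcome within arms. The size does not follow from the documents, because no loss rate is given.

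At low equal loss the distortion is small. A one-point imbalance at 1% to 2% loss is enough to triple the nominal error (7.7% against 2.5%) or to bring power down to about 74%. The 34% error and 29% power figures need a three-point imbalance. They illustrate sensitivity and are not a forecast for this trial. Because the rule governs a mortality claim and is the only handling stated, it should be changed before the data are analysed.

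**What to change.** In Statistical methodology:

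1. Make the primary estimate the 36-month mortality difference with censoring at the last date known alive (Kaplan-Meier with a Greenwood 95% CI), or an equivalent method valid under missing at random. The 5-point decision rule is unchanged.
2. Before analysis, complete vital status for randomized patients as far as possible, using the planned SNDS link if it holds dates of death. The article does not say whether it does.
3. Keep missing-equals-death only as a sensitivity analysis, beside a tipping-point analysis that varies the assumed mortality of missing patients separately by arm. Include the case least favourable to cessation: missing counted as dead in cessation and alive in continuation.
4. Report the number with missing vital status by arm.

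The cost is mainly a change of analysis wording, plus any work to obtain dates of death, with no added patients or visits. The small downside is that the primary estimate then assumes censoring at random, which the tipping-point analysis probes.
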